#### Data Source(s)

CCAE is an administrative health claims database for active employees, early retirees, COBRA continues, and their dependents insured by employer-sponsored plans (individuals in plans or product lines with fee-for-service plans and fully capitated or partially capitated plans). CCAE captures person-specific clinical utilization, expenditures, and enrollment across inpatient, outpatient, prescription drug, and carve-out services. It also includes results for outpatient lab tests processed by large national lab vendors. ~108 million patients are available in CCAE from 1/2000-10/2013.

MDCD contains the pooled healthcare experience Medicaid enrollees from multiple states. It includes inpatient services and prescription drug claims, as well as information on enrollment, long-term care, and other medical care. MDCD has ~16 million lives from 1/2006-12/2012.

Optum represents an administrative health claims database made mostly of members of United Healthcare, who are enrolled in commercial plans, Medicaid and Legacy Medicare Choice with both medical and prescription drug coverage. Optum captures person-specific clinical utilization, expenditures, and enrollment across inpatient, outpatient, prescription drug, and carve-out services. It also includes results for outpatient lab tests processed by large national lab vendors. Optum has ~36 million lives from 1/2006-12/2012.

CPRD contains anonymised longitudinal electronic health records from primary care practices in UK from 1987-present day. It is a patient management system with many aspects of patient care covered, including diagnoses, prescriptions, signs and symptoms, procedures, labs, lifestyle factors, clinical and administrative/social data. ~11.5 million patients are available in the database.

All databases are transformed to the OMOP Common Data Model (CDM) v4. Details about the OMOP CDM are available at: <http://omop.org/CDM>. One standard analysis program will be developed for this protocol, and executed consistently across all databases using the OMOP CDM.

## STATISTICAL METHODS

### Sample Size and Study Power

All qualifying patients will be included within each cohort for this descriptive summary. No statistical tests are being performed, so no sample size or study power calculations are required.

### Measurement

#### Exposure Definition and Measures

No exposures defined or measured for this protocol.

#### Outcome Definition and Measures

##### Concept Code List

One code set (used to gather patient pregnancy records) will be utilized for all data sources in order to determine pregnancy outcomes and markers, as the OMOP CDM allows for standardization of clinical content across all databases. All content (conditions, procedures and observations) in the OMOP CDM are referred to by concepts. The OMOP Standard Vocabularies are used to understand and make use of these concepts. Native source codes are mapped to the dictionary that is considered standard for that domain (conditions, procedures, etc.) in the Standard Vocabularies. For instance, Read condition codes from CPRD and ICD-9 condition codes from US claims databases are mapped to SNOMED-CT concepts in all of our CDM versions of the 4 databases. SNOMED_CT is the standard dictionary for conditions and LOINC is the standard dictionary for labs and observations in the CDM. There is no standard dictionary for procedures. Procedures will be identified by ICD-9 procedure, CPT-4, HCPCS and SNOMED-CT concepts.

Our pregnancy concept list was developed utilizing the OMOP Standard Vocabularies. SNOMED-CT concepts indicating pregnancy care, screening, outcomes etc. were identified and all descendants were gathered into one code list. Read and ICD-9 pregnancy chapter searches identified concepts not picked up by the SNOMED-CT concept search as the range and terminologies of pregnancy-related concepts are broad and some pregnancy concepts are descendants of non-pregnancy higher-level concepts. Hornbrook et al. [[1](#_ENREF_1)] shared the source code list used in their analysis using a US administrative claims data source and we also validated our concepts against their source codes.

The categorized pregnancy concepts that will be used to create the pregnancy episodes are specified below. At this time concepts that had 100 or more records in the data were categorized. Categorizing the remaining source codes and validation will improve the accuracy of the pregnancy episode algorithm.

The pregnancy outcomes will be defined with concepts from these categories (excepting premature, post-term and full-term concepts which will be used to infer pregnancy start dates):

| Premature | PREM |
| --- | --- |
| Post-term | POSTT |
| Full-term | FT |
| Live Birth (in multiple births at least one live birth) | LB |
| Stillbirth | SB |
| Induced or legal abortion | AB |
| Delivery-Live birth or stillbirth | DELIV |
| Spontaneous abortion | SA |
| Ectopic pregnancy | ECT |
| Trophoblastic disease | TRO |

Pregnancy markers at various stages of the pregnancy episode include these categories:

| Confirmation of pregnancy | PCONF |
| --- | --- |
| Antenatal GP visits | AGP |
| Pregnancy complication codes | PCOMP |
| Labor and pre-delivery codes | LDEL |
| Threatened abortion | TA |
| Postpartum | POST |

Screening tests include concepts from these categories:

| Alpha fetoprotein screening tests | AFP |
| --- | --- |
| Amniocentesis screening tests | AMNIO |
| Obstetrical ultrasound | ULS |
| Gestational Diabetes screening | DIAB |
| Other lab tests or procedures indicative of pregnancy | OTEST |

Calculations involving recordings of ‘last menstrual period’ or gestational age will use concepts from these categories:

| Gestational age indicated | GEST |
| --- | --- |
| LMP | LMP |

##### Summary of Pregnancy Episode Algorithm

The algorithm to determine pregnancy episodes will include several steps. In the first step, all pregnancy outcomes for a patient will be assigned. In the second step, pregnancy start dates will be assigned.

###### 1st Step in the Pregnancy Episode Algorithm: Assignment of Outcomes

An outcome assessment hierarchy rational was chosen similar to that used in a study by Mikolajcyzk et al. Births unambiguously indicate the outcome took place, however spontaneous abortions and ectopic pregnancies may only indicate suspicion of occurrence of the event so these will be assessed after birth outcomes [[11](#_ENREF_11)]. Valid outcomes will be assessed in this order:

- Live birth (at least one)
- Stillbirth
- Delivery-Live birth or stillbirth
- Trophoblastic Disease
- Ectopic pregnancy
- Induced abortion
- Spontaneous abortion

Before searching for outcomes, remove all patients from consideration who only have gestational diabetes screening (DIAB) records without any other pregnancy categories, as urine and serum glucose tests have low specificity for pregnancy.

Outcomes will be found in the CDM condition_occurrence, procedure_occurrence and observation files. In addition to SNOMED-CT and procedure concepts in the CPRD CDM:

- live births can be indicated by LOINC concepts when the value_as_string field in the observation table=’Live birth’ or ‘Neonatal death’
- stillbirths can be indicated by LOINC concepts when the value_as_string field in the observation table=’Still birth’ or ‘Intra-partum death’
- deliveries can be indicated by LOINC concepts when the value_as_string field in the observation table=’Unknown’

The following steps assign the valid pregnancy outcomes:

1. Valid live birth (LB) outcomes will be assessed first. Starting with the first LB outcome (assumed to be true), the 2^nd^ LB outcome will be assessed to see if it occurs after the necessary time interval (see Table 1). Table 1 contains time windows that are based on the least amount of time a 2^nd^ outcome can happen after the 1^st.^  These can change based upon the specific outcomes under consideration. Minimum time allowed between two LB outcomes is 182 days. These time windows were adapted from the Hornbrook et al.[[1](#_ENREF_1)] algorithm and validated by in-house medical experts. If the 2^nd^ LB outcome happens too soon after the 1^st^, it will be removed from consideration and the 3^rd^ LB outcome will be compared to the 1^st^ LB outcome in the same manner. If the 2^nd^ LB outcome occurs after the time window allowed it will be classified as a valid outcome, and the 3^rd^ LB outcome will be compared to it; this process will be repeated until all LB outcomes for a patient are assessed.
2. Next, all stillbirth (SB) outcomes will be assessed. The first SB outcome found for a patient will be compared to all LB outcomes determined to be valid for the patient in the prior step. If all LB outcomes prior to the SB outcome occur 168 days prior to the SB outcome and all LB outcomes after the SB outcome occur 182 days after the SB outcome then the first SB outcome will be added to the valid outcome set. Each subsequent SB outcome will be assessed for validity in this manner against all LB and SB outcomes that have been determined to be valid using Table 1 in the prior step. In other words, if all outcomes prior to the subsequent SB outcome are prior to the minimum number of days for that outcome combination in Table 1 and all outcomes after the subsequent SB outcome are after the minimum number of days for that outcome in Table1 then the subsequent SB outcome will be added to the outcome set.
3. Next, all delivery (DELIV) outcomes will be assessed against all valid LB, SB and DELIV outcomes in the same manner as described above for SB and added to the valid outcome set if Table 1 criteria is met.
4. Next, ectopic pregnancy (TRO) outcomes will be assessed against all valid LB, SB, DELIV, and TRO outcomes in the same manner as described above for SB and added to the valid outcome set if Table 1 criteria is met. In order to eliminate TRO rule-out diagnoses, if there is an antenatal GP visit, pregnancy confirmation or pregnancy complication record within 42 days of the TRO record that TRO outcome will not be added to the valid outcome set.
5. Next, ectopic pregnancy (ECT) outcomes will be assessed against all valid LB, SB, DELIV, TRO and ECT outcomes in the same manner as described above for SB and added to the valid outcome set if Table 1 criteria is met. In order to eliminate ECT rule-out diagnoses, if there is an antenatal GP visit, pregnancy confirmation or pregnancy complication record within 42 days of the ECT record that ECT outcome will not be added to the valid outcome set.
6. Next, induced abortion (AB) outcomes will be assessed against all valid LB, SB, DELIV, TRO, ECT and AB outcomes in the same manner as described above for SB and added to the valid outcome set if Table 1 criteria is met.
7. Next, spontaneous abortion (SA) outcomes will be assessed against all valid LB, SB, DELIV, TRO, ECT, AB, and SA outcomes in the same manner as described above for SB and added to the valid outcome set if Table 1 criteria is met. In order to eliminate SA rule-out diagnoses, if there is an antenatal GP visit, pregnancy confirmation or pregnancy complication record within 42 days of the SA record that ECT outcome will not be added to the valid outcome set.

| Table 1: Minimum Number of Days Required to Identify Separate Pregnancy Outcomes | | |
| --- | --- | --- |
| First Pregnancy Outcome | Second Pregnancy Outcome | Minimum Days Between Outcomes |
| LB | LB | 182 |
| LB | SB | 168 |
| LB | DELIV | 168 |
| LB | TRO | 70 |
| LB | ECT | 70 |
| LB | AB | 70 |
| LB | SA | 70 |
| SB | LB | 182 |
| SB | SB | 168 |
| SB | DELIV | 168 |
| SB | TRO | 70 |
| SB | ECT | 70 |
| SB | AB | 70 |
| SB | SA | 70 |
| DELIV | LB | 182 |
| DELIV | SB | 168 |
| DELIV | DELIV | 168 |
| DELIV | TRO | 70 |
| DELIV | ECT | 70 |
| DELIV | AB | 70 |
| DELIV | SA | 70 |
| TRO | LB | 168 |
| TRO | SB | 154 |
| TRO | DELIV | 154 |
| TRO | TRO | 56 |
| TRO | ECT | 56 |
| TRO | AB | 56 |
| TRO | SA | 56 |
| ECT | LB | 168 |
| ECT | SB | 154 |
| ECT | DELIV | 154 |
| ECT | TRO | 56 |
| ECT | ECT | 56 |
| ECT | AB | 56 |
| ECT | SA | 56 |
| AB | LB | 168 |
| AB | SB | 154 |
| AB | DELIV | 154 |
| AB | TRO | 56 |
| AB | ECT | 56 |
| AB | AB | 56 |
| AB | SA | 56 |
| SA | LB | 168 |
| SA | SB | 154 |
| SA | DELIV | 154 |
| SA | TRO | 56 |
| SA | ECT | 56 |
| SA | AB | 56 |
| SA | SA | 56 |

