###### 2nd Step in the Pregnancy Episode Algorithm: Assignment of Start Dates

In the pregnancy episode algorithm time periods need to be defined for various elements in order to calculate pregnancy start date. In Table 2 below the following time periods for each outcome are defined:

- Maximum pregnancy term - amount of time to search back from the outcome for all pregnancy markers. This time period should be the longest possible gestation period for an outcome so as to capture early markers.
- Minimum pregnancy term - Shortest possible gestational period for each outcome.
- Number of days a 2^nd^ pregnancy is possible after the outcome – This time window indicates how many days after the outcome specified another pregnancy may be initiated.

All time windows were estimated from research specific to each outcome and validated by in-house clinical experts.

| **Table 2: Time windows in days necessary to calculate pregnancy episode start date** | | | |
| --- | --- | --- | --- |
| **Outcome** | **Maximum Pregnancy Term** | **Minimum Pregnancy Term** | **Days 2nd pregnancy possible after outcome** |
| **LB** | 301 | 161 | 28 |
| **SB** | 301 | 140 | 28 |
| **DELIV** | 301 | 140 | 28 |
| **TRO** | 112 | 42 | 14 |
| **ECT** | 84 | 42 | 14 |
| **AB** | 168 | 42 | 14 |
| **SA** | 133 | 28 | 14 |

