1. If AFP date-123 exists between (larger of maximum term allowed subtracted from outcome date or prior outcome date plus retry count) and minimum term allowed subtracted from outcome date then AFP date-123 becomes the pregnancy start date.
2. If there are more than one AFP records in the allowed time window, use the first so as to use the AFP date that is most likely the recommended date in clinical guidelines rather than a repeat test.

**Step 5:** Outcome specific estimates:

1. If at least one PREM (premature term pregnancy), POSTT (post term pregnancy) or FT (full term pregnancy) record exists between (larger of maximum term allowed subtracted from outcome date or prior outcome date plus retry count) and 30 days after outcome date then categorize pregnancy as PREM, POSTT or FT.
2. If combinations of PREM, POSTT, FT records exist in this time window, categorize pregnancy in this order: 1) PREM if present, 2) POSTT if present, 3) FT if present.
3. Based on Table 4, choose an outcome specific gestational age estimate based on outcome and term and subtract from outcome date to obtain a pregnancy start date. If prior outcome date plus retry count is greater than outcome date minus outcome specific gestational age estimate then pregnancy start date becomes prior outcome date plus retry count.

**Step 6**: Choose final pregnancy start date:

1. Choose the best pregnancy start date (first one assigned in steps 1-5).
2. If a PCONF (pregnancy confirmation), AGP (antenatal GP visit) or OTEST (other pregnancy test) category records exist between (larger of maximum term allowed subtracted from outcome date or prior outcome date plus retry count) and minimum term allowed subtracted from outcome date and is prior to the best start date as calculated in the prior 5 steps then the first found PCONF, AGP or OTEST becomes pregnancy start date.

Table 4 provides outcome specific gestational age estimates for all outcomes for premature, post and full term pregnancies. These outcome specific gestational age estimates were obtained from Hornbrook et al.[[1](#_ENREF_1)] and Margulis et al. and were validated by in-house clinical experts and should represent average gestational times for the outcomes and terms.

| **Table 4: Outcome Specific Gestational Age Estimates in Days** | | | | |
| --- | --- | --- | --- | --- |
| **Outcome** | **PreTerm** | **PostTerm** | **FullTerm** | **NoData** |
| **LB** | 245 | 285 | 280 | 280 |
| **SB** | 196 | 285 | 280 | 196 |

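### Table 1's minimum gaps before a live birth are 7 days shorter than Table 2 implies, so Step 5 can assign live-birth episodes below the stated minimum term; the spontaneous-abortion gaps also differ, without explanation

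*Protocol*

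**What the plan says.** In the first step of the algorithm (Assignment of Outcomes), a candidate outcome is kept only if it is far enough in time from every outcome already accepted. The required gaps for all 49 ordered pairs of the seven outcomes are in Table 1, titled "Minimum Number of Days Required to Identify Separate Pregnancy Outcomes". The text explains their basis: "Table 1 contains time windows that are based on the least amount of time a 2^nd^ outcome can happen after the 1^st". Item 1 adds "Minimum time allowed between two LB outcomes is 182 days", and item 2 uses 182 days again for a live birth after a stillbirth.

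The second step (Assignment of Start Dates) defines the Table 2 columns. One is "Minimum pregnancy term - Shortest possible gestational period for each outcome". Of the last column it says: "This time window indicates how many days after the outcome specified another pregnancy may be initiated". For LB the minimum term is 161 days. The last column is 28 days after LB, SB or DELIV and 14 days after TRO, ECT, AB or SA.

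Under Pregnancy Episode Start Date Calculation, Steps 1–4 and the marker rule in Step 6 accept a start date only within a window. It opens at the later of outcome date minus maximum term and prior outcome date plus retry count, and closes at outcome date minus minimum term. Step 5 item 3 is the fallback when no such date is found: "If prior outcome date plus retry count is greater than outcome date minus outcome specific gestational age estimate then pregnancy start date becomes" the prior outcome date plus the retry count.

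**The concern.** The two tables describe the same timing constraints, one as gaps between outcomes and the other as their components. If they disagree, the first step can accept a pair of outcomes for which the second step has no valid start date. The Protocol then does not stop: Step 5 supplies a date and does not test it against the minimum term. The Exclusion Criteria remove episodes only for falling outside the observation period.

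This matters because the primary objective is to evaluate episode start, end and outcome, and the planned results are outcome counts and term distributions by outcome. One program runs on all four databases, so any inconsistency is repeated in each. No sensitivity analysis is planned.

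**Working it through.** **Inputs.** Table 1 (all 49 rows), Table 2 (minimum term and last column) and Table 4 (LB estimates of 245, 280 and 285 days). The term retry count is read as Table 2's last column, the only quantity in the Protocol that fits it. Table 2's columns run maximum term, minimum term, retry days, as in "DELIV | 301 | 140 | 28".

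**Formula.** Least gap = retry days of the first outcome + minimum term of the second.

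| Second outcome | Minimum term | 28 + term | Table 1 after LB, SB, DELIV | 14 + term | Table 1 after TRO, ECT, AB, SA | Table 1 minus sum |
|---|---|---|---|---|---|---|
| LB | 161 | 189 | 182 | 175 | 168 | −7 |
| SB | 140 | 168 | 168 | 154 | 154 | 0 |
| DELIV | 140 | 168 | 168 | 154 | 154 | 0 |
| TRO, ECT, AB | 42 | 70 | 70 | 56 | 56 | 0 |
| SA | 28 | 56 | 70 | 42 | 56 | +14 |

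Five second outcomes × 7 first outcomes = 35 rows agree exactly. Two second outcomes × 7 = 14 rows do not. Counting days inclusively or exclusively does not explain this: a shift of one day either way makes all 49 rows disagree. Read backwards, Table 1 implies a minimum LB term of 182 − 28 = 168 − 14 = 154 days (Table 2: 161), and a minimum SA term of 70 − 28 = 56 − 14 = 42 days (Table 2: 28).

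**Consequence for LB.** Let g be the days from the prior accepted outcome to the live birth, and count start dates from that prior outcome. For g below 301, g − 301 is negative, so the retry bound sets the earliest start.

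- After LB, SB or DELIV: earliest start 28, latest g − 161. The window is open only if g ≥ 28 + 161 = 189. At g = 182 the latest start is 21; at g = 188 it is 27. Both are before 28, so the window is empty.
- After TRO, ECT, AB or SA: earliest start 14, latest g − 161. The window is open only if g ≥ 14 + 161 = 175. At g = 168 the latest start is 7; at g = 174 it is 13. Again the window is empty.

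Steps 1–4 therefore assign nothing, and the Step 6 marker rule uses the same empty window. In Step 5 even the shortest LB estimate puts the start before the prior outcome (188 − 245 = −57), so the fallback always applies. Episode length is then g − 28 = 154 to 160 days after a birth, or g − 14 = 154 to 160 days after a loss. This is 1 to 7 days below the 161-day minimum.

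**Consequence for SA.** Table 1 rejects an SA at gaps of 56–69 days after a birth and 42–55 days after a loss, which Table 2 would allow. No impossible episode results. At Table 1's smallest SA gap after a birth, 70 days, the start window runs from 28 to 70 − 28 = 42. After a loss, at 56 days, it runs from 14 to 56 − 28 = 28. Both are open.

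**The case against.** The Protocol never says that Table 1 is calculated from Table 2. Table 1 was adapted from a published algorithm and Table 2 rests on research specific to each outcome; both were checked in-house. So no stated calculation is wrong. This stands: the point is an inconsistency between tables. The stated definitions nevertheless imply the sum, and 35 exact matches make coincidence implausible.

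For SA the objection is strong. Table 1 also serves to separate new events from repeat records, and the Protocol says that SA records may reflect only suspicion of the event. SA carries the same gap as TRO, ECT and AB, and has a 42-day rule-out condition of its own. A longer gap than the biological minimum may be intended. A reader might infer that early repeat losses are undercounted, but that would require the rejected records to be new pregnancies and not follow-up coding, which the documents do not show.

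A reader might also infer that the empty LB window discards a true LMP or gestational-age date. The documents do not support this either. At these gaps any start that satisfies the 161-day minimum falls before the retry point, so no date is valid under the Protocol's own rules. The second record may equally be a repeat record of the first birth.

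Finally, the bands are narrow, and the planned review of term distributions and of start-date plausibility could expose short episodes. Neither would prevent them.

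**Conclusion.** The LB inconsistency is a real defect of limited scope. All seven rows ending in LB are 7 days shorter than Table 2 implies. Within a 7-day band of gaps (182–188 days after LB, SB or DELIV; 168–174 days after TRO, ECT, AB or SA) the algorithm must produce an episode shorter than its own minimum term. If the requirement in item 1 that the interval has passed is read strictly, the band loses its first day (183–188 days, episodes of 155–160 days) and the defect remains.

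The seven rows ending in SA are 14 days longer than Table 2 implies. That is an unexplained difference, not a demonstrated error.

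The conclusion assumes that the retry count is Table 2's last column and that the stated definitions mean what they say. The documents give no frequencies, so the number of affected episodes is unknown. They also do not show which table is right.

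**What to change.** 1. Reconcile the LB rows of Table 1, and the 182-day figure in items 1 and 2, with Table 2's minimum LB term. Either table may be the one to change. Altering the retry days instead (to 182 − 161 = 21 and 168 − 161 = 7) would break all 35 rows that now agree.
2. After Steps 5 and 6, add a check that flags or removes any episode shorter than its outcome's minimum term, and report the count.
3. Either reconcile the SA rows with Table 2 or state in one sentence why the longer SA gap is intended.

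The cost depends on the choice. Changing Table 1 is a lookup edit, but it changes which outcomes are kept. Between two live births the later record drops out. For the other pairs it is the earlier outcome that drops out, because live births are accepted first and the rest are tested against them. Changing Table 2's LB minimum term instead moves the closing date of the start-date window for every LB episode in Steps 1–4 and 6, so those results would need to be rerun. The check in item 2 is a few lines of code and is worth having whichever table changes.

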**Commonly administered pregnancy screening tests**

It is feasible to use common pregnancy screening tests such as Alpha fetoprotein (AFP) usually administered within narrow gestational-age windows to determine start of pregnancy episode. An assessment in Optum of the accuracy of these screening tests in determining length of pregnancy episode was conducted and of the 4 most commonly performed tests in the table below, AFP and nuchal ultrasound produced enough accuracy. However, the second algorithm in Margulis et al. [[2](#_ENREF_2)] attempted to determine beginning of pregnancy with screening test claims such as alpha fetoprotein in live births and only 45.4% of estimated gestational age at birth were within 1 week of the hospital discharge estimate; they had better success with outcome-specific estimates. For this reason, in our algorithm, we will discard any AFP or nuchal ultrasound calculated start dates that create an episode shorter or longer than the minimum and maximum allowed episode for that outcome in Table 3.

| **Table 3: Median length of pregnancy episode in days when commonly administered pregnancy screening tests are used to infer episode start date** | | | | |
| --- | --- | --- | --- | --- |
| **Pregnancy screening test** | **Clinical gestational age at which test is recommended in weeks** | **Optum Gestational age used at date of test in weeks** | **Optum median length of pregnancy in days with start date calculated from screen test** | **Comment** |
| **Alpha fetoprotein** | 15-20 | 17.5 | 276.5 | present in 1/3 live births;Q3=284 days |
| **Amniocentesis** | 15-20 | 17.5 | 258 | too few done in population |
| **Nuchal ultrasound** | 11.5-13.85 | 12.65 | 279 | Present in 16% live births;Q3=285 days |
| **Gestational Diabetes screening** | 24-28 | 26 | 272 | glucose screenings done prior to 26 week screen;Q3=386 days |

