**Pregnancy Episode Start Date Calculation**

To calculate pregnancy episode start date possible start dates will be assigned in the following hierarchy (final start date chosen will be first one assigned in hierarchy):

**Step 1:** LMP (last menstrual period) date as start of pregnancy episode:

1. If LMP records exists between (larger of maximum term allowed subtracted from outcome date or prior outcome date plus retry count) and minimum term allowed subtracted from outcome date then LMP becomes the pregnancy start date
2. If there are more than one LMP records in the live birth window, use the latest so as not to grab a LMP record from an earlier pregnancy episode
3. ~50% of CPRD live births will have an LMP value (median pregnancy length 280 days using LMP date as start of episode); no US claims live births will

**Step 2:** GEST (gestational age in weeks) date as start of pregnancy episode:

1. In CPRD, for GEST record use string_as_value from observation table or in CPRD or US CLAIMS use gest_value from pregnancy concept file, whichever is present. Only use GEST values between 0 and 42 weeks.
2. If GEST record date-(GEST value*7) +1 exists between (larger of maximum term allowed subtracted from outcome date or prior outcome date plus retry count) and minimum term allowed subtracted from outcome date then GEST record date-(GEST value*7) +1 becomes the pregnancy start date.
3. If there are more than one GEST records in the allowed time window, use the latest so as not to grab a GEST record from an earlier episode
4. ~28% of CPRD live births will have a GEST value and not a LMP value with a median pregnancy length 279 days (in CPRD GEST codes are used for any outcome in the additional file); 1.4% of Optum live births will have a GEST value with a median pregnancy length 230 days (in OPTUM GEST codes are used primarily to record a premature birth)

**Step 3:** NULS (nuchal ultrasound) date as start of pregnancy episode:

1. If NULS date-89 exists between (larger of maximum term allowed subtracted from outcome date or prior outcome date plus retry count) and minimum term allowed subtracted from outcome date then NULS date-89 becomes the pregnancy start date.
2. If there are more than one NULS records in the allowed time window, use the first so as to use the NULS date that is most likely the recommended date in clinical guidelines rather than a repeat test.

**Step 4:** AFP (alpha fetoprotein test) date as start of pregnancy episode:

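### The rule-out test for suspected trophoblastic, ectopic and spontaneous-abortion records ignores later nuchal ultrasound and AFP records, so a suspected loss can be kept and shorten the live birth that follows

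*Protocol*

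**What the plan says.** The protocol's section on the 1st Step (Assignment of Outcomes) explains why a filter is needed: "spontaneous abortions and ectopic pregnancies may only indicate suspicion of occurrence of the event". Items 4 (TRO), 5 (ECT) and 7 (SA) then apply one. For ECT, the record is not accepted "if there is an antenatal GP visit, pregnancy confirmation or pregnancy complication record within 42 days of the ECT record". The markers are therefore AGP, PCONF and PCOMP, and no direction is given for the 42 days. Item 4 is parallel. Item 7 uses the same markers and window but ends: "within 42 days of the SA record that ECT outcome will not be added to the valid outcome set".

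The Concept Code List holds AFP, amniocentesis (AMNIO) and obstetric ultrasound (ULS) as separate categories. The section on commonly administered screening tests finds AFP and nuchal ultrasound accurate enough for dating, and Start Date Steps 3 and 4 use them for that. Table 3 gives their recommended timing and their frequency in Optum; for nuchal ultrasound the comment is "Present in 16% live births;Q3=285 days".

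An accepted loss then limits the next episode. In the start-date steps the earliest allowed date is the "larger of maximum term allowed subtracted from outcome date or prior outcome date plus retry count". Of the last column of Table 2, which is 14 days for TRO, ECT and SA, the protocol says: "This time window indicates how many days after the outcome specified another pregnancy may be initiated".

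**The concern.** The filter exists to remove losses that were only suspected. A nuchal scan or AFP test soon after the suspected loss points to the same pregnancy continuing, and the algorithm already extracts these records for dating. Leaving them out of the filter means that such a loss survives whenever none of the three named markers happens to be coded nearby.

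Two errors follow. One pregnancy is counted as two episodes, the first a false loss. The live birth that follows is also cut short, because the false loss becomes its prior outcome and pushes the earliest allowed start date forward. Outcome counts, the outcome distribution and pregnancy terms by outcome are what the Descriptive Analyses section says the study will produce, and all three are affected.

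**Working it through.** **Inputs.**
- Table 1: at least 168 days from TRO, ECT or SA to LB (a gap of exactly 168 is taken as accepted).
- Table 2: LB maximum 301 and minimum 161 days; ECT maximum 84 and minimum 42; last column 14 days for TRO, ECT and SA.
- Table 3: nuchal ultrasound at 11.5-13.85 weeks (12.65 used); AFP at 15-20 weeks (17.5 used).
- Table 4: LB 280 days at full term or with no term data, 245 if preterm.
- Assumption: the retry count is the last column of Table 2.

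**The protocol's own offsets.** 12.65 x 7 = 88.55, rounded to 89 (Step 3). 17.5 x 7 = 122.5, rounded to 123 (Step 4). Both reproduce.

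**Could a test within 42 days after a loss belong to a new pregnancy?** The earliest new pregnancy starts at loss + 14 days.
- Nuchal: 14 + 11.5 x 7 = 14 + 80.5 = 94.5 days after the loss.
- AFP: 14 + 15 x 7 = 14 + 105 = 119 days after the loss.

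Both lie well beyond 42 days, so a test done in its recommended window cannot.

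**Worked case.** LMP day 0, ECT code day 49, nuchal scan day 89, live birth day 280, no AGP, PCONF or PCOMP record within 42 days of the code.
1. Rule-out: the scan is 89 - 49 = 40 days after the code but is not a listed marker. The ECT is kept.
2. Table 1: 280 - 49 = 231, at least 168. Both outcomes stand.
3. Start of the ECT episode: allowed from 49 - 84 = -35 to 49 - 42 = 7. The true LMP (day 0) falls inside, so the false loss takes it.
4. Start of the LB episode: lower limit is the larger of 280 - 301 = -21 and 49 + 14 = 63, so 63; upper limit 280 - 161 = 119. The LMP (day 0) and the nuchal-based date (89 - 89 = 0) are both rejected.
5. Step 5: 280 - 280 = 0 is before day 63, so the start becomes day 63.
6. Step 6 has the same lower limit and cannot move the start earlier.
7. LB length: 280 - 63 = 217 days instead of 280, a loss of 63 days.

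Without an LMP, as in US claims, the LB result is the same, because the nuchal-based date is rejected too.

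**General form, birth at day 280.** Start = s + 14, so length = 280 - (s + 14) = 266 - s. Table 1 requires 280 - s to be at least 168, so s is at most 112.

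| Loss code, day s | LB length, days |
|---|---|
| 42 | 224 |
| 56 | 210 |
| 70 | 196 |
| 84 | 182 |
| 112 | 154 |

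For s = 106 to 112 the length is 160 to 154 days, below the LB minimum of 161 in Table 2. For a preterm birth at day 245 the length is 231 - s with s at most 245 - 168 = 77: 189 days at s = 42 and 154 at s = 77.

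**Reach of a 42-day rule that counts these tests.**
- Nuchal window, days 80.5 to about 97: loss codes from 80.5 - 42 = 38.5, about day 39, to day 97.
- AFP window, days 105 to 140: loss codes from 105 - 42 = day 63. An AFP at day 123 reaches only codes from 123 - 42 = day 81.

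In the worked case the nuchal scan would cancel the ECT and the birth would regain 280 days. An AFP test alone would not.

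**The case against.** The strongest objection concerns frequency. The error needs a false loss code, no AGP, PCONF or PCOMP record within 42 days, and a later test. Because the 42 days have no stated direction, they can be read as either side of the code: days 7 to 91 in the worked case. A woman who goes on to a nuchal scan and a term birth with none of the three markers in that span may be uncommon. The protocol gives neither the false-loss rate nor the share lacking these markers. This stands.

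A reader might add Table 3's 1/3 (AFP) and 16% (nuchal) and infer that roughly a third to a half of pregnancies are affected. The protocol does not support that: these are frequencies of tests in Optum live births, not error rates, and no CPRD frequency is given.

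A reader might also infer that these tests are the best available proof of continuation. The protocol never compares them with the three listed markers. It judges them for dating, and even there it cites an outside study with only 45.4% of test-based estimates within one week.

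A further objection is that any choice of markers trades false losses against rejected true ones. That has force against long windows. It has little against tests dated after the loss and within 42 days, since in their recommended windows they cannot come from a new pregnancy.

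Finally, the Validation Procedures section has clinical personnel check outcome and start date, and Study Limitations admits outcome misclassification. The review can reveal such errors in CPRD and Optum, but it does not correct the rule and does not sample CCAE or MDCD.

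**Conclusion.** The point holds as a defect in the rule with an unknown number of affected episodes. When it occurs, the following live birth loses s + 14 days: 63 days for a loss code at day 49, with a false loss counted as well. No later step repairs this. The result rests on three assumptions: the retry count is the last column of Table 2, a 168-day gap is accepted, and the tests were done in their recommended windows.

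Table 1 already removes loss codes after day 112 before a birth at day 280, and after day 77 before a birth at day 245. Amniocentesis matters little, since Table 3 notes that too few are done.

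Item 7 should not be read as already working in the same way for SA. Its markers and window match, but as written it removes an ECT outcome, so no SA record is ever ruled out. Adding markers there has no effect until that wording is corrected.

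**What to change.** - In items 4, 5 and 7, add nuchal ultrasound and AFP to the rule-out evidence, counted only when dated after the loss record and within the existing 42 days. The direction matters because a test before a true loss is to be expected. Amniocentesis is optional.
- Give nuchal ultrasound its own entry in the Concept Code List. Step 3 uses NULS, but the list shows only ULS; general obstetric ultrasound should stay out of the rule.
- Correct item 7 so that it removes the SA record.
- Define the retry count as the last column of Table 2, if that is what is meant.

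Windows of up to 94 days (nuchal) and 118 days (AFP) follow from the 94.5 and 119 days above. They could be examined as a sensitivity check but should not be the main rule, because at their edges an off-schedule test in a new pregnancy could reject a true loss.

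The cost is a few lines of code on records that the start-date steps already use. The remaining downside is that a test done off schedule, or for a reason other than pregnancy, could occasionally reject a true loss. Loss codes before about day 39 would still depend on the three existing markers.
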